#### *Study length and estimated sample size:*

MC services will be offered at the selected two sites for 1 year. The estimated cost per circumcision is \$40. We expect to recruit five clients per week at each site for a total convenience sample of 500 subjects in one year (250 per site). During the second year of the project, we will continue to assess behavioral risk factors for the first six months and work on analyzing the data during the last semester of the project.

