An aliquot of the patient's serum (2 mls) will be preserved for future testing at the University of Illinois. As long as the investigators hold personal identifiable information, participants will be informed of the results of any future testing performed on their blood and will be offered treatment free of charge and referrals as outlined above. Section d.3 provides a complete description of how these samples will be managed, preserved and transported. Urine will not be preserved for future testing.

If there is a temporary, medically curable condition present, such that it would be advisable to defer potential surgery, then the participant will be treated and asked to return for re-evaluation for study eligibility when he is cured. Men found to have an STD or to be HIV-positive will be referred for immediate care. Once enrollment is completed, participants will be given an appointment for the surgery.

Circumcision will be performed soon after informed consent, preferably within a few days. All surgeries will be done under local anesthesia in a clinic by trained clinicians, using the standardized forceps-guided method described by Krieger and colleagues and contained in the WHO MC manual. Circumcised men will be counseled to refrain from sex for six weeks post-surgery and counseled about risk of HIV infection through open wounds during the healing process. They will be checked for complications and asked about their sexual activity seven days after the procedure. Men without complications will be followed six months after surgery with behavioral risk assessment, HIV testing and counseling. Men may come to the study sites for unscheduled visits at any time during the 6 month follow-up. All men will be counseled at enrollment and all follow-up visits to reduce their risk for HIV infection by consistent condom use and, where applicable, reductions in numbers of sex partners. Counselling on condom use and sexual risk reduction will be provided by trained, experienced, native-speaking counsellors.

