## Timeline

| Activity                                       | Months |   |   |   |   |   |   |   |   |    |    |    |    |    |    |    |    |    |    |    |    |       |
|------------------------------------------------|--------|---|---|---|---|---|---|---|---|----|----|----|----|----|----|----|----|----|----|----|----|-------|
|                                                | 1      | 2 | 3 | 4 | 5 | 6 | 7 | 8 | 9 | 10 | 11 | 12 | 13 | 14 | 15 | 16 | 17 | 18 | 19 | 20 | 21 | 22-24 |
| Development of educational material            | X      |   |   |   |   |   |   |   |   |    |    |    |    |    |    |    |    |    |    |    |    |       |
| Training of providers                          |        | X | X |   |   |   |   |   |   |    |    |    |    |    |    |    |    |    |    |    |    |       |
| Recruitment of participants and Implementation |        |   | X | X | X | X | X | X | X | X  | X  | X  | X  | X  | X  |    |    |    |    |    |    |       |
| Acceptability and uptake                       |        |   | X | X | X | X | X | X | X | X  | X  | X  | X  | X  | X  |    |    |    |    |    |    |       |
| Safety and adverse AEs                         |        |   | X | X | X | X | X | X | X | X  | X  | X  | X  | X  | X  | X  | X  | X  | X  | X  | X  | X     |
| Sexual behaviors                               |        |   | X | X | X | X | X | X | X | X  | X  | X  | X  | X  | X  | X  | X  | X  | X  | X  | X  | X     |
| Analysis of data                               |        |   |   |   |   |   |   |   |   |    |    |    |    |    |    | X  | X  | X  |    |    |    |       |
| Preparation of manuscripts                     |        |   |   |   |   |   |   |   |   |    |    |    |    |    | X  | X  | X  | X  | X  | X  | X  | X     |
| Prepare R-O1 application                       |        |   |   |   |   |   |   |   |   |    |    |    |    |    |    |    |    |    |    | X  | X  | X     |

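### The study-length text and the timeline give different end dates for behavioural follow-up and different analysis periods, and the timeline's analysis row closes before its own data collection ends

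*Protocol*

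**What the plan says.** **Text (Protocol, Study length and estimated sample size).** Recruitment: "MC services will be offered at the selected two sites for 1 year", and "We expect to recruit five clients per week at each site for a total convenience sample of 500 subjects in one year (250 per site"). Project year two: "we will continue to assess behavioral risk factors for the first six months and work on analyzing the data during the last semester". In project months, behavioural assessment ends at month 18 and analysis occupies months 19-24.

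**Timeline (end of the Protocol).**
- "Recruitment of participants and Implementation": marked in months 3 to 15, which is 13 monthly cells. Month 3 is also marked for provider training.
- "Sexual behaviors" and "Safety and adverse AEs": both marked from month 3 through the 22-24 column.
- "Analysis of data": marked in months 16, 17 and 18 only.

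**Follow-up of each man (Specific aim #3, Subject recruitment).** "Men without complications will be followed six months after surgery with behavioral risk assessment, HIV testing and counseling".

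**The concern.** The two places cannot both be followed. They disagree on when behavioural follow-up ends (month 18 against months 22-24) and on when the data are analysed (months 19-24 against 16-18). Taken alone, the Timeline schedules collection for up to six months after its last marked analysis month.

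The six-month visit matters because it is the only scheduled visit after day 7. Under Outcomes and in the adverse event table, torsion, erectile problems and psycho-behavioural problems are sought only at the later time point. The sexual behaviour outcome compares baseline with six months and is the basis for aim 5 and its hypothesis of no difference. Satisfaction is also asked at day 7, but satisfaction once the man has healed and resumed sex comes from the six-month questionnaire.

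If staff took month 18 as the cut-off, the men without a six-month record would be the last enrolled as a group. They would not be a random subset, so ordinary missing-data reasoning would not cover the gap well.

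**Working it through.** **Inputs.** Target 500 men; 5 per week at each of 2 sites; 1 year of services (text). Recruitment in months 3-15; analysis in months 16-18; behaviour and safety rows to months 22-24 (Timeline). Six months of follow-up per man. Surgery follows consent within days, so that lag is taken as zero. Even accrual is my assumption.

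**1. The plan's own figure.** 5 × 2 × 50 working weeks = 500, which matches. With 52 weeks it would be 520.

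**2. When the last six-month visits fall.** Last recruitment month + 6.
- Recruitment to month 15: 15 + 6 = 21.
- Recruitment for 12 months from month 3 (to month 14): 14 + 6 = 20.

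**3. Windows side by side.**

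| Item | Text | Timeline |
|---|---|---|
| Recruitment | 1 year | months 3-15 |
| Behavioural assessment ends | month 18 | months 22-24 |
| Analysis | months 19-24 | months 16-18 |

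The last visits (month 20 or 21) come after the text's end of behavioural assessment and after the Timeline's analysis row. They fall within the Timeline's collection rows and within the text's analysis window.

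**4. Share without a six-month visit by the end of month 18.** A man reaches six months by then only if he was circumcised by the end of month 12 (18 − 6 = 12).

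| Recruitment assumption | Share after month 12 | Men of 500 |
|---|---|---|
| Even over months 3-15 | 3/13 = 23.1% | about 115 |
| 12 months, mid-month 3 to mid-month 15 | 2.5/12 = 20.8% | about 104 |
| 12 months, months 3-14 | 2/12 = 16.7% | about 83 |
| 10 per week from the start of month 3 until 500 | 1 − (10 months × 52/12 weeks × 10)/500 = 1 − 433.3/500 = 13.3% | about 67 |
| Months 1-12 (text taken alone) | 0% | 0 |

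**5. When the Timeline's analysis opens.** At the start of month 16, men circumcised in months 10-15 have not reached six months: 6/13 = 46%, about 231 of 500 under even accrual over 13 months.

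**6. Can recruitment start in month 1?** The sections on aims 1 and 2 make educational materials the first phase, with ethics approval before distribution, and provider training the second. The Timeline puts these in months 1-3. The 0% row therefore does not fit the protocol's own sequence.

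**The case against.** A reader might infer that 23% of men would miss the six-month analysis. The documents do not support that. No section locks the database or drops men at month 18, and the six-month visit is defined from surgery with no calendar limit. The Timeline's collection rows run past month 21, and the text's analysis window covers month 21. If collection followed the Timeline and analysis followed the text, nobody would be lost through scheduling. The text ends only behavioural assessment at month 18; it does not end safety follow-up. And 23% is the top of a range that depends on accrual.

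The text also has a coherent reading of its own: one service year, six more months of assessment, then analysis. If its second year is counted from the start of services in month 3, assessment runs to month 20 and covers a 12-month intake. Analysis would then occupy months 21-26, which overruns the 24-month Timeline. If it is counted in project months, services would have to start in month 1.

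Two further inferences should be avoided. Thirteen marked cells need not contradict one year of services, since a year beginning partway through month 3 touches 13 cells. Nor would results after a month-18 cut rest only on the cases of newly trained providers, because everyone circumcised in months 3-12 would be included.

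What remains is that the rescue requires taking half of each of two conflicting schedules, and nothing in the protocol tells staff to do so.

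**Conclusion.** The inconsistency is real and visible on the page: two end dates for behavioural follow-up, two analysis windows, and a Timeline whose only analysis row closes before its collection rows do. With recruitment starting in month 3 and lasting about a year, the last six-month visits fall in month 20 or 21. The consequence is conditional. Only if six-month data were cut at month 18 would about 13-23% of men (67-115 of 500) lack the six-month assessment. That range rests on even accrual, a month-3 start, the full 500 being reached and no other loss to follow-up. Following the longer window in each place brings the scheduling loss to zero. This is a moderate consistency repair in a pilot study, not evidence of planned attrition, but it is worth making before recruitment because it protects the late complications and the aim 5 comparison.

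**What to change.** Put one schedule in both places.
- Study length paragraph: state the recruitment window in project months. Say that six-month visits and behavioural assessment continue until the last enrolled man reaches six months (about month 21), and that the final six-month analysis follows in months 22-24.
- Timeline: split the analysis row. Keep months 16-18 for uptake, operative and day-7 outcomes, and add months 22-24 for the six-month outcomes.

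The change costs one sentence and one Timeline row, with no extra visits and no change in sample size. The downside is timing: preparation of the grant application is marked from month 20 through 22-24, so the six-month results would reach it only late in that period. Uptake, operative and day-7 results would still be ready earlier.

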#### Specific aims #4 and #5:

##### *Circumcision Procedure*

Prior to surgery, the clinician will obtain a complete medical history and perform a physical exam (form 3).

A brief description of the procedure follows. The patient lies on his back in a comfortable position. The pubic area is shaved clean with a disposable razor and the hair is picked up with a dressing tape. The surgeon scrubs up and puts on 2 pairs of sterile gloves. The client's skin is prepared with Betadine solution, making sure that the inner surface of the prepuce and the glans are clean and the skin is dry. The outer pair of gloves is then removed. The client is draped with two drapes and a center "O" towel, and then, using 2% lidocaine without epinephrine, a dorsal nerve block and a field block

with special attention to the ventral nerve, is performed. Normally, no more than 10ml of 2% lidocaine will be used. The anesthetic effect of the nerve block is checked, and revised if necessary. The prepuce is held with two mosquito forceps, one on each lateral aspect, then a curved mark is made with sterile disposable marking pens, outlining the planned surgical cut. The mark is made one cm proximal to the coronal sulcus all round, and parallel to the coronal sulcus. The prepuce is clamped along the mark with a Kocher clamp while retracting the glans, ensuring that the glans itself is not clamped. The prepuce is excised using a surgical blade along the mark. Bleeders are identified, clamped and tied. They are sutured, and if necessary ligated, using 3/0 plain catgut. After ligating all the bleeders, the area is irrigated with normal saline and then inspected for more bleeders, which are identified and tied. Using 3/0 chromic catgut on a taper 4/8 circle needle, a U-shaped horizontal mattress stitch is made on the ventral side of the penis (frenulum) to join the skin at the "V" shaped cut, which is then tied and tagged with a mosquito forceps. Using vertical mattress stitches, four quarters are tagged, and a vertical mattress stitch added, after which a simple stitch is put at the center of every two mattress stitches (a total of at least 16 stitches). The area is irrigated with normal saline and other simple stitches added as required. The wound is dressed with Sofratulle, then with a regular dressing bandage and a strapping. The client is advised to rest for 30 minutes, and if stable, discharged home on mild analgesics. Upon completion of the procedure the surgeon completes a procedure form (form 4). The excised foreskin tissue is taken to the laboratory with no identifiers, discarded with other laboratory waste, and incinerated with other biological waste within three days.

Participants will be given verbal and written instructions on postoperative wound care and counseled to refrain from sexual activity for at least six weeks after the procedure. They will also be encouraged to come to the clinic or contact a clinician at any time with medical problems.

#### Follow- up study visits

Participants will be offered the equivalent of US\$ 5.00 for each scheduled study visit to cover travel expenses.

#### *Day 7 Post Circumcision Visit (form #5)*

Circumcised men will be asked to return to the clinic 7 days after the procedure to check the wound, to see if it is healing properly, to check for complications, and to ask about their sexual activity, their level of pain, resumption of work or other activities, and their satisfaction with the procedure and care at the clinic. As with all visits, any adverse events will be recorded. Blood and urine will be collected for STD testing at this visit.

### *Six month post operative visit (form #6)*

During this visit a brief exam to confirmed proper wound healing will be performed. A behavioral and satisfaction questionnaire will be administered.

A semi-structured qualitative interview will be conducted to explore in-depth the lived experience of male circumcision. Interviews will be conducted by a trained qualitative researcher using a semi-structured guide in a private location at the clinic. Participants will be asked about their satisfaction with the procedure, perceptions about post-operative sexual performance, partner satisfaction and sexual risk behaviors, among other topics (Appendix B). Probing techniques will be used to elicit in-depth and detailed accounts of personal experiences and perceptions following circumcision and to limit socially desirable responses. Field notes will be used to provide additional insight into the context of the interview and any important non-verbal communication.

Qualitative data analysis will be iterative, starting with the completion of the first interviews and continuing throughout the data collection process. All transcripts will be analyzed in Spanish. Transcripts will be read multiple times by the study team to identify key themes and stories. A list of analytical codes will be developed based on the themes that emerge from the interview transcripts and the transcripts will be coded using the Atlas.ti software. The outputs of the coding exercises will be used to prepare matrices for the analysis of patterns across the study population and for comparisons between sub-groups (for example, older men vs younger men, married vs single). Memo writing will be integrated throughout the process to facilitate the interpretation of the data and to provide an audit trail of the analysis that can be used to document how the data were interpreted. Socio-demographic data will be summarized using SPSS to provide a descriptive sample of the study population.

Researchers at the University of North Carolina will be involved in this qualitative data collection and analysis. All data obtained and shared among performance sites will be de-identified. The names of the participants will not be recorded to protect their confidentiality.

### *Unscheduled Follow-up Visits*

*Ad hoc* clinic visits will be encouraged to check and treat for complications of the procedure. At such visits, medical examinations and laboratory testing will be conducted as indicated, and appropriate treatment provided free of charge. Medical referral will be made if required.

### Outcomes

The primary objectives of the proposed study are to assess the uptake, safety (adverse event rate) and patient satisfaction, train providers and build capacity on VMMC in the Dominican Republic. In addition, we will assess risk behaviors before and after VMMC and build key partnerships with the MoH of the DR and other stakeholders, which will

help develop a proposal to the NIMH to conduct operational research in the context of larger scale provision of MC services.

The study will assess the number of patients who undergo the procedure and the degree of post-operative satisfaction.

We will also record immediate complications of the circumcision procedure, which include: 1) pain, 2) excessive bleeding, 3) anesthetic-related complications, 4) excessive skin removal and 5) damage to the penis. Early post-surgical complications will include the occurrence of any of the following within one month of the procedure: 1) pain, 2) excessive bleeding, 3) excessive skin removed, 4) insufficient skin removed, 5) swelling or hematoma, 6) damage to the penis, 7) infection, 8) delayed wound healing, 9) problem with the appearance of the penis, and 10) problems with voiding.

The following complications will be evaluated at six months after the procedure: 1) infection, 2) delayed wound healing, 3) problem with the appearance of the penis, 4) excessive skin removed, 5) insufficient skin removed, 6) torsion of the penis, 7) erectile function problems, and 8) psycho-behavioral problems. In addition to the 8-day and six month post-surgery visits, men will be encouraged to come to the clinic for an unscheduled visit at any time they have excessive pain, they have bleeding, they detect an infection, or they desire treatment for any reason. Complications will be recorded at those unscheduled visits as well. See the sections on Adverse Events and Reporting Adverse Events below for more detail.

*Sexual behavior* will be another important outcome, particularly as there is concern that men who are circumcised may mistakenly feel that they are protected from HIV and may adopt more risky sexual behavior. On the other hand, sexual activity among circumcised men is likely to be much less for a period of time following the circumcision, which will decrease risk during that period. Self-reported sexual behavior (e.g. number of sex partners, lifetime, last 12 months and last 6 months; sex for gifts or money; condom use) will be assessed at baseline and at 6 months with a standard set of questions. We will also ask participants directly about their perceptions of change in risk for HIV acquisition.

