### **a) Specific Aims:**

Based on the results of numerous observational studies and the three RCTs the World Health Organization (WHO) and the Joint United Nations Programme on HIV/AIDS (UNAIDS) have endorsed VMMC as a biomedical intervention for HIV prevention. As such, countries with a high prevalence of HIV in the population are encouraged to examine the feasibility of offering MC services as part of the portfolio of HIV prevention strategies at a national level. The specific aims for this project are:

- 1) To develop culturally appropriate education materials about the benefits of VMMC for clients attending pilot healthcare centers.
- 2) To train a core group of providers on proper surgical and counseling techniques to provide comprehensive VMMC services.
- 3) To determine the acceptability, uptake and demand for MC services in key areas of high HIV prevalence.  
H1: The acceptability and uptake among high risk men will be around 60%.
- 4) To assess the safety and adverse events of performing circumcision in resource constrained settings.  
H2: VMMC will result in a complication rate of less than 2%.
- 5) To assess sexual risk behaviors, perceptions of sexual function and sexual pleasure in men before and after VMMC. H3: there will be no differences in risk behaviors, sexual function and pleasure after VMMC
- 6) Estimate point prevalence of most common STI in a subset of circumcised men and preserve a small sample of blood to test future scientific hypothesis and/or newer testing techniques as they become available.
- 7) To build collaborations with the MoH and other partners in the DR and at UIC to develop a proposal to NIMH for operational research in the context of larger scale MC service provision.

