#### Specific aims #3 and #4:

Patient satisfaction with VMMC will be assessed at every postoperative visit. Forms 6 and 7 ask clients about their satisfaction or dissatisfaction with the procedure and their partners acceptability of their VMMC. Subjects will also be asked if they have recommended VMMC to other men. If so, we will record and estimate the most common reason for recommending the procedure to their peers. Other outcomes to be recorded and analyzed include: number of men requesting VMMC by age; number circumcised by age and marital status; proportion circumcised who are HIV tested and counseled; time and personnel involved in each surgery; proportion of circumcisions with moderate and severe AEs by day of ascertainment, and proportion of men who resume sex before 42 days post-surgery.

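### The one-month complication window has one scheduled visit, at day 7, and the protocol contradicts itself on whether men with complications are followed at six months

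*Protocol*

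**What the plan says.** **Window.** The Outcomes section of the Protocol states: "Early post-surgical complications will include the occurrence of any of the following within one month of the procedure". Ten event types follow.

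**Visits.** The Day 7 section says: "Circumcised men will be asked to return to the clinic 7 days after the procedure to check the wound". The Outcomes section gives the same visit a different day: "In addition to the 8-day and six month post-surgery visits". The next scheduled visit is at six months. Between the two, men are encouraged to come in unscheduled, and complications found then are recorded.

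**Six-month population.** The Subject recruitment section under Specific aim #3 says: "Men without complications will be followed six months after surgery with behavioral risk assessment, HIV testing and counseling". The Outcomes section introduces the six-month list without that condition: "The following complications will be evaluated at six months after the procedure". The six-month visit section (exam and satisfaction questionnaire) and the sexual-behaviour paragraph under Outcomes set no such limit either.

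**Target and measure.** H2 in the Specific Aims is that "VMMC will result in a complication rate of less than 2" per cent. The analysis section for aims 3 and 4 reports the "proportion of circumcisions with moderate and severe AEs by day of ascertainment". The sample is fixed by expected recruitment: "We expect to recruit five clients per week at each site for a total convenience sample of 500 subjects in one year".

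**The concern.** A complication rate defined over a month but actively sought once, a week after surgery, can miss events that start later or occur in men who do not come back. Missed events lower a rate taken over all circumcisions, which is the direction that favours H2. Safety is a primary objective, and the threshold is low enough for a handful of events to matter.

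The six-month wording raises a different problem. If only men who healed without trouble are assessed at six months, then later satisfaction, sexual function and risk behaviour (H3) are measured in a selected group. Patient satisfaction is also a primary objective. An analysis plan cannot recover data that were never collected.

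**Working it through.** **1. The protocol's own figure.** Five clients a week × 2 sites × 50 weeks = 500, which reproduces the stated sample. A full 52 weeks would give 520. The protocol states no power, attendance or dropout figure to check.

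**2. Coverage of the window.** Taking a month as 30 days, 30 − 7 = 23 days follow the only scheduled visit, and 23/30 = 77%. This is a share of calendar time. It is not a share of risk, since many surgical events occur in the first week.

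**3. Can the six-month visit fill the gap?** Comparing the two lists in the Outcomes section:

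- On both lists: appearance, infection, slow healing, too much skin removed, too little skin removed.
- On the early list only: pain, bleeding, swelling or hematoma, penile damage, voiding problems.

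The severity table in the Adverse Events section shows the same split. Its post-surgical part also has wound dehiscence, which its one-month-or-more part lacks. If one of the five types arises in days 8 to 30 in a man who does not return, no listed six-month item captures it.

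**4. Possible size, for post-operative events only.** Let d = attendance at day 7 × share of events visible by then, and u = share of the remaining events recorded at unscheduled visits. Then

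observed rate = true rate × [d + (1 − d)u].

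Both d and u are assumptions. With 80% attendance and 80% of events visible, d = 0.8 × 0.8 = 0.64. The last column is the binomial chance of 9 or fewer events in 500.

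| u | captured | true 2% reads as | true 3% reads as | chance of observing under 2% if truth is 3% |
|---|---|---|---|---|
| full ascertainment | 1.00 | 2.00% | 3.00% | 6.7% |
| 0.9 | 0.964 | 1.93% | 2.89% | 8.6% |
| 0.5 | 0.82 | 1.64% | 2.46% | 21% |
| 0 | 0.64 | 1.28% | 1.92% | 51% |

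Over attendance of 70–100%, visibility of 60–100% and u of 0–0.9, the captured fraction runs from 0.42 to 1.00.

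**5. Sensitivity of H2.** Ten events in 500 give 2.0% (95% CI 0.96% to 3.65%). At most 4 events keep a one-sided 95% upper bound below 2%, and at most 3 do so for a two-sided 95% interval. A few unseen events could change the conclusion.

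**6. The six-month restriction.** Suppose each man counts once for any complication. Men dropped for having had a complication are already in the numerator, and the event-free men who could still become cases are kept. That rate does not fall. What is lost is further or late outcomes in the dropped men, and their six-month satisfaction, function and behaviour.

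**The case against.** Unscheduled visits are encouraged throughout, treatment is free, and complications are recorded at them. The analysed outcome is moderate and severe events, and several of those grades are defined by a return, re-exploration, re-operation or referral. Passive reporting should catch such events best. At u = 0.9 the distortion is small: a true 2% reads as 1.93%. This stands, and it is why no single size can be given. It is not complete protection, because a man treated elsewhere, or not at all, may never be graded.

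The sentence about men without complications may only mean that such men need no visit before six months. It mentions behavioural assessment, HIV testing and counselling, while the six-month complication list stands elsewhere without restriction. Satisfaction is also asked at day 7. That milder reading is plausible, but the text does not say it, and the sections need to agree.

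A reader might infer that men never examined are counted as event-free, because the measure is a proportion of circumcisions. The protocol does not say so. The phrase goes on to refer to day of ascertainment, which also fits visit-specific reporting, and the Adverse Events section has presence or absence recorded at visits. Denominators may properly be left to an analysis plan, which is not shown here.

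Time to resumption of sex is already asked at follow-up, and the forms are not shown, so some checklist items may already exist.

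**Conclusion.** Two points hold on the text. First, the one-month window has one scheduled visit, and half of its event types have no place on the six-month list. The post-operative complication rate is therefore at risk of underestimation by an unknown amount. The table above illustrates the range under assumed attendance and capture, and is not an estimate for this trial. Events during surgery are recorded on the day and are outside the concern.

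Second, the sections disagree on who is followed at six months. Taken literally, the restrictive wording would bias six-month satisfaction, sexual function and risk behaviour favourably, assuming that men with complications fare worse on them.

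It is tempting to conclude that both features push the complication rate down. The documents do not support that for the six-month wording, for the reason in step 6. Nor do they support a firm statement that the rate is biased low by a given amount.

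**What to change.** - Reconcile the Subject recruitment, six-month visit and Outcomes sections (including the sexual-behaviour paragraph) so that six-month data collection covers every circumcised man, with or without complications.
- Make the day-7 and day-8 references agree.
- Add to the six-month form a dated recall checklist of all ten early event types, plus wound dehiscence from the severity table. Include any care sought elsewhere in days 8 to 30, and the date of first sex if not already asked.
- Report attendance at each visit, the complication rate among men examined beside the rate among all circumcised, and events found at scheduled and unscheduled visits separately.

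The cost is revised wording, a slightly longer existing form and a second denominator in the tables. Recall at six months of events in days 8 to 30 is imperfect, so the checklist narrows the gap and does not close it. The reported rate may rise.
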